### Recruitment {15}

Participants will be recruited as part of daily general practice, as outlined above. There are no additional strategies to ensure adequate recruitment.

## Assignment of interventions: allocation

### Sequence generation {16a}

Allocation of control and intervention groups will be done by simple balanced randomization (1:1), meaning that there will always be an equal number of control and intervention practices, assigned randomly. Enrolment of practices will be based on the in- and exclusion criteria described above and will be performed by researcher A, who is part of the trial. This will generate a numbered list of the eligible practices. Researcher B will then, independently and on a separate form, assign numbers (denoting a specific practice) to either the control or intervention groups by means of a computer-generated list of random numbers, i.e., simple randomization (for example, by using the website random.org to generate random numbers within a specified interval).

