### Trial design {8}

This study will be a cluster randomized trial: primary care practices will be randomized and divided into a control and intervention group. Allocation of control and intervention groups will be done by simple balanced randomization (1:1).

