## Methods: Participants, interventions, and outcomes

### Study setting {9}

This study will take place in the eligible Flemish primary care practices in the INTEGO network.

The INTEGO network is a morbidity registry containing coded contents of the electronic health records of some 400,000 patients from 100 general practitioner’s offices all over Flanders. The information is automatically collected during daily practice and contains diagnoses, year of birth, gender, prescriptions, lab results, and various biomedical parameters such as blood pressure, height, weight, etc. [1]. The INTEGO procedures have been validated by the Belgian Privacy Commission. The registry is hosted on the Healthdata platform (www.healthdata.be) [28].

Patients coming to the eligible practices, as well as the practices themselves, will be recruited separately. They will fill in separate consent forms. After consent is given by the patient, the GPs of the recruited practices will explain the study outline and specific details, such as the installation and use of the app, at the first consultation, after which the study period for that specific patient will commence. General care will proceed as normal.

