### Sample size {14}

The calculation hereafter is similar to that of an earlier paper, comparable to ours [34]. We used an online calculator, which can be found at http://www.sample-size.net/sample-size-proportions.

The sample size calculation was performed for the primary outcome (AF detection rate at practice level). In the INTEGO database, we found a baseline AF incidence of 13.65/1000 patients, 65 years or older, in 2015. As stated above, we estimated a realistic absolute increase of 24.57 AF cases per 1000 patients per year in the intervention group. The power calculation, with a power of 0.80 and an α of 0.05, for a two-sided two-sample *t* test, with the incidence of AF per 1000 patients per year as the outcome variable, led to a sample size of 1835 patients in each arm of the study.

As we will view the results on the practice level, the number of practices needs to be determined, considering the intra-cluster correlation coefficient (ICC). A similar study found an ICC of 0.0027 (18). As we plan to let this study run for 12 months, we wish to include 400 patients (= *m*) per practice/physician. Calculating the variance inflation factor (1 + ICC (*m* – 1)) leads us to a value of 2.077. To accommodate the expected variance, we will have to include 1835 × 2.077, or 3811 patients per arm. We will assume a loss to follow-up of 15% [32]. This brings us to a total study population of 8765 patients, or approximately 11 control and 11 intervention practices.

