### Implementation {16c}

All Flemish primary care practices in the INTEGO network conforming to the inclusion criteria will be contacted for inclusion in the study. Then, they will be randomly subdivided into intervention and control practices by the method described above. There will be an equal amount of intervention and control practices. In every practice, patients will be selected according to the previously defined in- and exclusion criteria, mentioned above. Later, high-risk patients in the intervention groups will be identified using the CHARGE-AF score, and will be prescribed the FibriCheck® app. High risk is defined as a 5-year risk of AF of at least 10% according to this score. The GPs in the intervention practices will explain the study outline to these patients and instruct them how to use the app, after which the study period begins for those patients.

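### The 22 practices are split 11:11 at random without using any practice information: this is valid, but it gives up precision and credibility that restricted allocation on registry data would buy cheaply.

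*Protocol article*

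**What the plan says.** Sequence generation {16a} describes "simple balanced randomization (1:1), meaning that there will always be an equal number of control and intervention practices". The same paragraph then says that numbers are assigned to arms "by means of a computer-generated list of random numbers, i.e., simple randomization". Trial design {8} and Implementation {16c} repeat the 1:1 split, and Sample size {14} plans "approximately 11 control and 11 intervention practices". The number of practices is the only thing balanced.

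On order, enrolment by researcher A comes first: "This will generate a numbered list of the eligible practices". Implementation {16c} agrees: "Then, they will be randomly subdivided into intervention and control practices by the method described above".

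On available data, Study setting {9} says of INTEGO: "The information is automatically collected during daily practice and contains diagnoses, year of birth, gender, prescriptions, lab results". Sample size {14} takes the AF incidence in patients 65 or older from that database.

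The analysis in Statistical methods {20a} is a cluster-level t test with inverse-variance weighting. No covariate is named, and {20b} rules out additional analyses. Table 2 lists neither prior AF rate nor practice size among the baseline characteristics.

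**The concern.** With 11 units per arm, chance alone can leave the arms visibly different in the characteristic that matters most here, the practice's underlying AF rate. A reader who sees such a difference will discount the result, even though the test remains valid. The information needed to limit it appears to exist before the envelopes are prepared, and the described analysis does not adjust for it afterwards. Once practices are allocated, the design can no longer be improved.

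There is also a wording problem. Simple randomization normally means independent draws, which do not guarantee equal numbers, yet the same paragraph guarantees them. Researcher B needs one unambiguous procedure.

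**Working it through.** **Inputs.** From Sample size {14}: baseline p = 0.01365, ICC = 0.0027, m = 400 per practice, 11 practices per arm. From Outcomes {12}: a 2-fold increase, which is an effect of 13.65/1000.

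**The protocol's own figures.** A two-sided, continuity-corrected comparison of 0.01365 with 0.02730 at 80% power gives 1833 per arm, against 1835 stated. The design effect is 1 + 0.0027 × 399 = 2.077; 1835 × 2.077 = 3811; 2 × 3811 × 1.15 = 8765; 8765/400 = 21.9, so 22 practices. The 2-fold reading is therefore the one that reproduces the sample size.

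**Size of chance imbalance under 11:11.**
- Between-practice SD = √(0.0027 × 0.01365 × 0.98635) = 6.03/1000.
- SD of the arm difference in mean true rate = 6.03 × √(2/11) = 6.03 × 0.426 = 2.57/1000.
- Median absolute difference = 0.6745 × 2.57 = 1.7/1000; 95% range ±1.96 × 2.57 = ±5.0/1000.
- Fifth of baseline = 2.73/1000; 2.73/2.57 = 1.06; two-sided normal tail 29%.
- A simulation of 40,000 draws with gamma-distributed practice rates gave SD 2.58 and 29%.

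**Dependence on the effect meant.** Sample size {14} calls 24.57/1000 an absolute increase, but 24.57 = 1.8 × 13.65, so it may be a level. The chance that the imbalance exceeds a quarter of the effect is:

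| Effect per 1000 | Quarter | Chance |
|---|---|---|
| 10.92 (24.57 − 13.65) | 2.73 | 29% |
| 13.65 (2-fold) | 3.41 | 18% |
| 24.57 (as an increase) | 6.14 | 2% |

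**Dependence on the ICC.** Over an assumed range of 0.001 to 0.01, the chance of exceeding 2.73/1000 runs from 8% to 58%.

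**What restriction could achieve** (4,000 runs per simulation; assumed three prior years at 400 patients per practice per year, and stable practice rates; ranges are from two separate simulations):

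| Allocation | SD per 1000 | Chance above a quarter of 13.65 |
|---|---|---|
| Unrestricted | 2.5 to 2.6 | 18 to 19% |
| Two strata at the median | 1.9 to 2.1 | 9 to 10% |
| Constrained, best 10% of allocations | 1.25 to 1.27 | under 1% |

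If about 30% of practices change rate, constrained allocation reaches only about 2.0/1000. Pairing on a single prior year gives 1.84/1000.

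**What this means for precision** (baseline rate in both arms).
- Variance of a practice's observed rate, per 1000 squared: between 6.03² = 36.4; within 13,464 × 0.9973/400 = 33.6. The between share is 52%.
- Multiplied by 2/11, these become 6.61 + 6.10 = 12.71, so the standard error of the arm difference is 3.57/1000. The design-effect route gives the same: √(2 × 0.013464 × 2.077/4400) = 3.57/1000.
- With the between component cut to 1.3² = 1.69, the standard error is √(1.69 + 6.10) = 2.8/1000. With 2.0² = 4.0, it is √(4.0 + 6.10) = 3.2/1000.
- The reported standard error shows this gain only if the analysis adjusts for the balancing variables. The degrees of freedom spent are not included.

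**Practice size.** The protocol gives no spread. With an assumed coefficient of variation of 0.3, 0.5 or 0.7, the total list sizes of the arms differ by more than 1.25-fold in 8%, 29% or 45% of draws.

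**The case against.** The strongest reply is that unrestricted 11:11 allocation is a legitimate design and that its cost is already paid. The 2.57/1000 is the same between-practice variance that the factor 2.077 covers, and the cluster-level test protects the type I error. This stands in full: there is no bias and no unbudgeted error.

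Two stronger readings are tempting and should be resisted.
- A reader might infer that a sizeable imbalance is likely. The figures do not say so: at the protocol's ICC, about seven draws in ten stay within a fifth of the baseline rate, and about four in five stay within a quarter of a 2-fold effect.
- A reader might take the simple-randomization label literally and expect unequal arms. Independent draws would give 11:11 only 17% of the time and 8:14 or worse 29% of the time. The protocol rules this out by fixing equal numbers in {8}, {16a} and {16c}. The label is loose; it is not evidence of an 8:14 risk.

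It is also fair to say that the benefit of restriction is a best case. That INTEGO can supply each practice's prior AF rate and 65+ list size is an inference from {9} and {14}, not a statement in the text. The Discussion itself stresses that the study depends on complete coding, so a prior coded rate may partly measure coding habits. On practice size, {14} and {20a} plan for equal clusters of about 400, and nothing in the protocol shows how far real lists depart from that.

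What remains is that allocation uses no practice information and no adjustment is described, so a gain that appears to be available is left unused.

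**Conclusion.** The point holds as an efficiency and credibility recommendation, together with a correction of wording. It is not a validity defect. The chance difference between arms in true baseline AF rate has an SD of about 2.6/1000, with about a 3 in 10 chance of exceeding a fifth of the baseline rate. These figures rest on the protocol's ICC of 0.0027 and on 11 practices of equal weight per arm. The 18% for a quarter of the effect rests also on the 2-fold reading, and {12} and {14} leave a range of 2% to 29%.

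Restriction with adjustment would lower the standard error of the arm difference from about 3.6/1000 to between 2.8 and 3.2/1000, depending on how stable practice rates and coding are.

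**What to change.** - In Trial design {8} and Sequence generation {16a}, specify restricted 11:11 allocation, by two strata or by covariate-constrained randomisation, on the pre-trial INTEGO AF rate in patients 65 or older and the size of the 65+ list.
- Draw it with a seeded program from the completed list of practices, identified by number only.
- In Statistical methods {20a}, adjust the cluster-level analysis for the balancing variables, and add both to Table 2.
- Replace the simple-randomization wording in {16a} with a description that matches the fixed 11:11 split.

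Cost: one registry query, a short script, coded practice-level covariates supplied to researcher B (who now works only with practice numbers), and one or two degrees of freedom in the analysis. The envelope procedure and patient recruitment stay as they are. The change has to be made before the allocation planned for around November 2021.

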### Concealment mechanism {16b}

Researcher B will prepare sealed, opaque envelopes containing a paper that assigns a specific practice number to a study group, based on this randomly generated number sequence. The process of the envelope preparation up until sealing and storage in a locked compartment will be videotaped by researcher B, who will thereafter be excluded from every other aspect of the trial. Allocation papers should never be visible, only the envelopes and the numbers on them. The video will be stored on an external device, which will be put in the locked compartment.

After practice enrolment, researcher A will access the locked compartment with the envelopes and review the accompanying video to ensure proper envelope preparation. Without opening or tampering with the letters, researcher A will write the appropriate mailing address on the respective envelope, based on their numbered list of practices. The envelopes will only be opened by the practices if they have an unbroken seal. This protocol is adapted from Radford et al. [35].

### Implementation {16c}

All Flemish primary care practices in the INTEGO network conforming to the inclusion criteria will be contacted for inclusion in the study. Then, they will be randomly subdivided into intervention and control practices by the method described above. There will be an equal amount of intervention and control practices. In every practice, patients will be selected according to the previously defined in- and exclusion criteria, mentioned above. Later, high-risk patients in the intervention groups will be identified using the CHARGE-AF score, and will be prescribed the FibriCheck® app. High risk is defined as a 5-year risk of AF of at least 10% according to this score. The GPs in the intervention practices will explain the study outline to these patients and instruct them how to use the app, after which the study period begins for those patients.

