### Objectives {7}

The primary objective of this study will be to investigate the effect of a case-finding strategy with the FibriCheck® smartphone application on the detection rate of AF in comparison with opportunistic screening (i.e., pulse palpation, followed by an ECG) in patients with a high risk of AF in general practice. The secondary objective is to keep track of thrombo-embolic complications, death, and compliance with measurements.

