#### Control group

In every cluster designated as a control group, patients aged 65 or older will be selected according to the criteria outlined above. The difference here is that patients will be given only the standard opportunistic screening. This is the current best practice [31].

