### Outcomes {12}

#### Primary outcome measures

##### Detection rate of AF in patients 65 years and older

The detection rate of AF in both the control and intervention group will be calculated after 4 weeks. A significant difference in both groups will be noted. Compared with previous studies of similar design [32–34], we will realistically assume a 2-fold increase in the detection rate of AF in the intervention group to be significant.

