### Participant timeline {13}

The study will be conducted over the course of 12 months in general practices in the Flanders region of Belgium, planned to run from January 2022 to December 2022.

Allocation of control and intervention practices is planned to start around November 2021. Eligible participants will be followed in their usual primary care practice, and are recruited by the participating physician when they visit for whatever reason. They will be provided an information leaflet, a consent form, and 1 week decision time.

Participants will be followed for a total of 4 weeks. Measurements and other data will be collected and interpreted at the end of this period. After the total study period of 12 months, the resulting data will be analyzed.

A schematic overview of the timeline can be found in Table 1. A visual representation of the study flow can be found in Fig. 1.

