#### Data collected on demographics and clinical characteristics

To be able to compare both groups in terms of clinical similarity, we will provide relevant data that allows a reasonable comparison between the intervention and control groups. The data will be extracted from the medical software each practice uses by using the INTEGO procedures. The results will be analyzed and presented on the level of the practice. Baseline group characteristics relevant for the study will be assessed at the start of the study (Table 2).

**Table 2 Tab2:** Collected data on group characteristics (for control and intervention groups)

Group characteristics (***n*** = 22)	
Mean age Gender distribution Mean body mass index Mean systolic/diastolic blood pressure, heart rate Smoking status (current, former, never) Antihypertensive medication Type II diabetes Heart failure Myocardial infarction	

If not already present in the patient file, missing data will be collected during this first interview. For example, if there is no mention of a patient’s blood pressure or height and weight, the participating physician will measure these parameters and put them into the EHR.

The general group characteristics schematized in Table 2 will be used to calculate the cardiovascular CHARGE-AF risk score of patients in the intervention group.

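### The CHARGE-AF high-risk step is applied only in intervention practices after allocation is known, and under either denominator the text allows, the comparison does not answer the stated objective

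*Protocol article*

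**What the plan says.** All places are in the protocol article.

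- **Order of steps.** Eligible practices are contacted; "Then, they will be randomly subdivided into intervention and control practices by the method described above" (Implementation {16c}). Patients are selected afterwards and "are recruited by the participating physician when they visit for whatever reason" (Participant timeline {13}). Who will be blinded {17a} confirms that physicians and patients know the arm.
- **Common criteria.** Eligibility criteria {10} gives one list for both arms: age, a medical record, consent and the exclusions. It contains no risk criterion.
- **Intervention arm.** "Later, high-risk patients in the intervention groups will be identified using the CHARGE-AF score, and will be prescribed the FibriCheck® app". The cut is given there too: "High risk is defined as a 5-year risk of AF of at least 10% according to this score". Intervention description {11a} says that the patients found to be high-risk are then told about the study, and those interested consent and receive the app.
- **Where the score is calculated.** The baseline variables "will be used to calculate the cardiovascular CHARGE-AF risk score of patients in the intervention group" (Data collected on demographics and clinical characteristics).
- **Control arm.** Patients 65 or older are selected by the general criteria. "The difference here is that patients will be given only the standard opportunistic screening" (Control group).
- **Target population.** The objective is a comparison "in patients with a high risk of AF in general practice" (Objectives {7}). The primary outcome is "Detection rate of AF in patients 65 years and older" (Outcomes {12}). Sample size {14} uses 13.65 per 1000, the INTEGO incidence in all patients 65 or older.

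**The concern.** CHARGE-AF predicts AF, and AF detection is the primary outcome. If the score decides who enters one arm and not the other, that arm has a higher AF rate before anyone opens the app. Practice-level randomization cannot remove this, because the selection comes after it and is made by physicians who know their allocation.

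The objective, the outcome, the planning rate and the people invited also describe different populations. The document never says plainly which patients form the denominator of the practice-level detection rate. The answer decides whether the trial is biased or underpowered.

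**Working it through.** **Reproducing the plan's own figures.** A two-proportion calculation (Fleiss, continuity-corrected, two-sided 0.05, power 0.80) for 13.65 against 27.3 per 1000, the two-fold increase in Outcomes {12}, gives 1833 per arm; the plan states 1835. The design effect is 1 + 0.0027 × 399 = 2.077. Then 1835 × 2.077 = 3811 per arm, and 3811 × 1.15 × 2 = 8765. So the plan rests on the all-65+ rate in the control arm.

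**Reading A: the denominator is enrolled participants.**

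1. Control rate: 13.65 per 1000 per year.
2. Rate at the cut, assuming the score is calibrated in this population: 1 − (1 − 0.10)^(1/5) = 20.9 per 1000 per year.
3. Ratio with no app effect: 20.9 / 13.65 = 1.53. Dividing 10% by 5 gives 20.0 and a ratio of 1.47. Patients at the cut have the lowest risk among those selected, so about 1.5 is a floor.
4. Chance of a significant result in the app's favour when the app does nothing: 11 practices per arm, m = 340 (400 less 15%) to 400 patients each, ICC 0.0027, t test on 20 df, with
 SE = √{[p₁(1−p₁) + p₂(1−p₂)] / (11m) × [1 + 0.0027(m−1)]}.
 For m = 400, SE = 0.00400 and (0.02085 − 0.01365) / 0.00400 = 1.80. The non-central t then gives 40%; m = 340 gives 38%.
5. Sample size {14} works in annual rates, but detection is calculated after 4 weeks. Multiplying both rates by 28/365.25 leaves the ratio unchanged and makes events far rarer.

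| Mean 5-year risk of those enrolled | Rate per 1000 per year | Ratio to 13.65 | False positive in app's favour, annual rates | Same, 4-week rates |
|---|---|---|---|---|
| 10% (at the cut) | 20.9 | 1.53 | 38–40% | about 7% |
| 12.5% (assumption) | 26.4 | 1.93 | 77–80% | 11–12% |
| 15% (assumption) | 32.0 | 2.34 | 95–97% | 17–18% |

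The intended figure is 2.5%. As a cross-check, a two-proportion calculation at the effective size of 1835 per arm gives 32% for 20.0 and 39% for 20.9 per 1000 per year.

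**Reading B: the denominator is all eligible patients 65 and over.** The arms are then comparable, but only a share s of the intervention arm is offered the app. Suppose s = 0.5 (an assumption; the document gives no share) and the planned absolute gain occurs only in that share:

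- Gain 24.57 − 13.65 = 10.92: arm rate 13.65 + 0.5 × 10.92 = 19.1 per 1000; power 25–27%.
- Gain 27.3 − 13.65 = 13.65: arm rate 13.65 + 0.5 × 13.65 = 20.5 per 1000; power 35–37%.

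These use the same formula and annual rates. If instead the app doubled a high-risk baseline of 20.9, the gain would be 0.5 × 20.9 = 10.4 per 1000 and power about 63–66%. Dilution is then milder but still below the planned 80%.

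**The case against.** The strongest reply is that the score does not define the arms at all. The criteria list is common to both and has no risk item. Implementation {16c} selects patients in every practice by that list and brings in the score afterwards. Intervention description {11a} finds high-risk patients within the 65+ group and has app users' files flagged, which suggests that some intervention patients do not get the app. The outcome and planning rate are for 65+, and Statistical methods {20a} analyses everyone whether or not they received the screening. On that reading the filter does not confound the arms.

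This stands as a possible reading, but not as a cure. Other text points the other way: it is the high-risk patients who are told of enrolment, both arms must consent, every participant is asked to measure at least twice a day, and the analysis set is participants. If the all-65+ reading is meant, dilution and the mismatch with the objective remain.

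Two further objections also stand. The annual-rate false-positive figures are not the only defensible ones, because follow-up is 4 weeks. And calibration of a score built on US cohorts is not documented for Flemish registry incidence.

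A reader might also take the Control group wording, that the difference lies in the screening, to mean that controls pass the same risk step. The criteria it refers back to contain none, and two sections confine the score to the intervention group.

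**Conclusion.** The point holds as a defect under either denominator. The risk step exists only in the intervention arm, follows open allocation, and does not match the populations named in the objective, the outcome and the planning rate.

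- With enrolled participants as the denominator, the arms differ at baseline by a ratio of about 1.5 or more. At the cut, the false-positive chance is about 38–40% on annual rates or about 7% on 4-week rates, and higher if mean risk exceeds the cut. This assumes calibration of the score.
- With all eligible 65+ patients as the denominator, power is about 25–37%, assuming half are high-risk and the planned absolute gain is confined to them, on annual rates. The high-risk objective is not answered.

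A reader might infer that confounding is certain and that a useless app would succeed in most such trials. The documents do not support that. The denominator is ambiguous, and the largest percentages need both annual rates and assumed mean risks well above the cut. What is established is that neither reading gives a fair, adequately powered comparison in high-risk patients.

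**What to change.** State one denominator and apply it identically in both arms: 65 or older, no exclusion, and the protocol's own CHARGE-AF threshold. Calculate it from data already in the EHR or INTEGO in all practices before the allocation envelopes are opened, with one rule for missing score inputs. Enrol control and intervention patients only from that list and analyse that set.

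Amend Control group, Outcomes {12}, Implementation {16c} and the section on demographic and clinical data to match. In Sample size {14}, replace 13.65 per 1000 with the rate in high-risk patients over the time window actually analysed.

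Costs:

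- Recruitment had not started at the time of the article, so this is mainly wording and one data extraction per practice.
- The Discussion says some software cannot search every score parameter, and the plan collects missing inputs at the first consultation, after allocation. The common missing-data rule therefore has real work to do.
- Consent is still sought by physicians who know the arm. Analysing the whole list, including non-consenters, would close that gap, but it dilutes the effect and needs ethics confirmation.
- The sample size must be restated, with a check that practices hold 400 high-risk patients each.
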